### Sample size calculation

We will enrol 48 patients to test the hypothesis that patient dose distributions are improved with the use of the KIM technology. The derivation follow: treating each treatment session as an independent event and then using Simon’s two-stage design, a sample size of 24 sessions with intervention events will give us 90% power with 95% confidence to rule in a success rate of 2/3 in favour of the futile rate of 1/3. To obtain an estimated 24 treatment sessions with intervention events we need 24/0.10 = 240 treatment sessions, which for the 5-session SBRT regime equals 48 patients. The null hypothesis will be rejected if 16 or more responses are observed in 48 patients. This design yields a type I error rate of 0.0488 and power of 0.91 when the true response rate is 67%.

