**Fig. 1 Fig1:**
[figure not shown]
The SPARK study schema

For each treatment session for each patient, the accumulated patient dose distributions (Fig. 2) and the targeting accuracy (Fig. 3) will be determined via paired control by comparing the measured dose and targeting error with KIM to those that would have been present in the absence of KIM.

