### Objectives

The primary objective is to quantify accumulated patient dose distributions with the KIM intervention compared to dose distributions estimated without the KIM intervention. Secondary objectives are to assess patient treatment outcomes, to perform a technology assessment of KIM to quantify the clinical practice impact, and to assess KIM cancer targeting accuracy.

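### The hypothesis concerns patients' accumulated dose, but the powered test measures success only among sessions in which KIM intervened

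*Protocol article*

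**What the plan says.** The Objectives section sets a patient-level question: "The primary objective is to quantify accumulated patient dose distributions with the KIM intervention compared to dose distributions estimated without the KIM intervention". Methods/Design lists better patient dose distributions as the first of three hypotheses, and the Sample size calculation section ties the number of patients to that hypothesis: "We will enrol 48 patients to test the hypothesis that patient dose distributions are improved with the use of the KIM technology".

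The derivation that follows changes the unit. It proceeds by "treating each treatment session as an independent event" and states that "a sample size of 24 sessions with intervention events will give us 90% power with 95% confidence". The two rates being distinguished are 1/3 (futile) and 2/3 (success). The patient number is obtained by inflating for sessions without an intervention: "we need 24/0.10 = 240 treatment sessions, which for the 5-session SBRT regime equals 48 patients". The Analysis section keeps the same unit at the interim look, with about 10 intervention events expected in 100 sessions and possible stopping for futility at four or fewer responses.

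The rejection sentence at the end of the Sample size calculation section breaks with this. It requires at least 16 responses and gives 48 patients as the denominator.

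Measurement is broader than the test. Methods/Design, after Fig. 1, plans the comparison of dose with and without KIM throughout the trial: "For each treatment session for each patient, the accumulated patient dose distributions (Fig. 2) and the targeting accuracy (Fig. 3) will be determined via paired".

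**The concern.** Two quantities are treated as one. The first is the change in a patient's dose accumulated over five fractions, defined for all 48 patients. The second is the proportion of sessions counted as a response, among only those sessions in which KIM triggered a correction. The article states its objective and hypothesis in terms of the first and takes its error rates from the second.

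A high proportion of the second kind is compatible with a small average change of the first kind, because it says nothing about how many patients had a correction or how much dose each correction restored. If the null is rejected and the result is reported in the words of the hypothesis, the headline claim goes further than the test. A yes/no count also cannot answer an objective that asks for quantification.

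**Working it through.** **Inputs (protocol article).** From Sample size calculation: null rate 1/3, target rate 2/3, 24 intervention sessions, intervention rate 0.10, five sessions per patient, rejection at 16 or more, type I error 0.0488, power 0.91. From Analysis: 10 events at the interim, futility at 4 or fewer.

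**Step 1: patient number.** 24 / 0.10 = 240 sessions, and 240 / 5 = 48 patients. This reproduces the plan.

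**Step 2: which test has the stated error rates.** For a two-stage binomial design with n1 = 10, continuation if more than 4 respond, total n = 24 and rejection at r or more:

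P(reject | p) = sum over x = 5 to 10 of P(X1 = x) × P(X2 ≥ r − x), with X1 ~ Bin(10, p) and X2 ~ Bin(14, p).

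| Rule | Type I error | Power |
|---|---|---|
| 10 then 24 sessions, r = 12 | 0.0488 (p0 = 0.333); 0.0492 (p0 = 1/3) | 0.910 (p1 = 2/3); 0.915 (p1 = 0.67) |
| 10 then 24 sessions, r = 13 | 0.0233 (p0 = 1/3) | 0.885 (p1 = 2/3) |
| 10 then 24 sessions, r = 16 | 0.0008 (p0 = 1/3) | 0.588 (p1 = 2/3) |
| Single stage, 16 of 48 patients | 0.554 (p0 = 1/3) | above 0.999 (p1 = 2/3) |

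With the article's own 10 and 24 events, only the cut-off of 12 reproduces both stated figures. Read literally, with patients as the denominator, the rule has a type I error of 0.55. The stated properties therefore belong to a test conditional on intervention sessions.

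**Step 3: what a rejection covers.** Twelve responding sessions are 12 / 240 = 5% of all planned sessions and lie in at most 12 of 48 patients (25%). With the printed cut-off of 16, the figures are 16 / 240 = 6.7% and at most 16 of 48 patients (33%).

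**Step 4: patients without any intervention (scenario).** Assume couch shift only, independent sessions as in the derivation, and intervention rate q per session. Then P(no intervention in five sessions) = (1 − q)^5.

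| q | (1 − q)^5 | Patients of 48 |
|---|---|---|
| 0.10 (planning rate) | 0.590 | 28.3 |
| 0.20 (assumed here) | 0.328 | 15.7 |
| 0.30 (assumed here) | 0.168 | 8.1 |

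Under couch shift, a patient with no correction has the same dose with and without KIM. If interventions cluster within patients, fewer patients have one: at q = 0.10, the number with at least one falls from 19.7 of 48 under independence to about 17, 13 and 10 at assumed within-patient correlations of 0.1, 0.3 and 0.5.

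**The case against.** The strongest reply is that conditioning on interventions is legitimate. Under couch shift, a session without a correction is a tie between the two doses and carries no information on whether corrections help. Setting ties aside is ordinary in paired testing. Nor does improved patient dose have to mean that most patients improve, since a mean can shift because of a minority. This stands, and it is why the session test can be kept. It does not make the conditional result an answer to a question stated in patients' accumulated dose.

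A second reply is that the objective is one of estimation, that paired dose is to be determined for every session of every patient, and that its summary belongs in a fuller document. This also stands in part. A reader might infer that the data from sessions without an intervention are left out of the trial's conclusions. The article does not say so: it commits to collecting them and does not describe how they will be reported. The point rests only on the mismatch between the stated hypothesis and the stated test.

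A reader might also infer that most patients' dose will be unchanged. The article does not support that as a general statement. The Treatment delivery section allows MLC tracking, with continual adjustment of the beam, and also allows lower action thresholds and more frequent corrections. It gives no split between the two methods, and 10% is a planning figure. Under MLC tracking the dose may differ from the no-KIM estimate in any session, and it is then unclear what an intervention event is.

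**Conclusion.** The point holds as a mismatch between question and test. Objective and hypothesis concern patients' accumulated dose. The error rates of 0.0488 and 0.91 are those of a test on about 24 intervention sessions with a cut-off of 12, and the rejection sentence attaches a different count to a different denominator. A rejection would show that corrections often help when made; it would not by itself establish or size a patient-level dose benefit.

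The figure of about 28 of 48 patients without an intervention illustrates the gap. It depends on couch shift only, the 10% rate and independence between sessions, and it drops to about 16 or 8 at assumed rates of 20% or 30%. The mismatch itself depends on none of these. The data are not compromised; what needs correcting is the claim attached to the test.

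**What to change.** 1. Keep the session test, but state its hypothesis and its conclusion as success among sessions with an intervention.
2. Make the rejection sentence consistent with the derivation, using intervention sessions as the denominator and a cut-off that gives the stated error rates. With 10 then 24 events, that cut-off is 12.
3. State what counts as an intervention event for the test when MLC tracking is used.
4. As the answer to the primary objective, report the mean paired difference (KIM minus estimated no-KIM) in five-fraction accumulated dose across all 48 patients, including those with no intervention, with a 95% confidence interval across patients.
5. Name one metric as primary in advance, for example PTV D95%, and treat the others as supportive. Table 2 lists these metrics as planning constraints, so their use as delivered-dose endpoints has to be stated.

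The cost is wording in the protocol and analysis plan. No further patients or measurements are needed for the estimate, because paired dose is already planned for every session, although its precision with 48 patients has not been worked out here. The downside is that the all-patient effect will look smaller than the conditional success rate.

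### The stated type I error of 0.0488 and power of 0.91 assume independent sessions, although sessions are nested in patients; both are too favourable if responses correlate within patient

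*Protocol article*

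**What the plan says.** The Sample size calculation section proceeds by "treating each treatment session as an independent event" and describes "using Simon’s two-stage design, a sample size of 24 sessions with intervention events". The targets are "90% power with 95% confidence", to "rule in a success rate of 2/3 in favour of the futile rate of 1/3". An intervention event is expected in 10% of sessions, so "we need 24/0.10 = 240 treatment sessions, which for the 5-session SBRT regime equals 48 patients".

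The decision rule is printed as "The null hypothesis will be rejected if 16 or more responses are observed in 48 patients". The operating characteristics follow: "This design yields a type I error rate of 0.0488 and power of 0.91 when the true response rate is 67" per cent.

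The Analysis section places the interim look after 20 patients, when about 10 events are expected. Four or fewer responses may lead to stopping for futility. The article mentions no within-patient correlation, design effect or sensitivity range, and it names no model for the final test.

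**The concern.** A patient's five sessions share one anatomy, one treatment plan, one set of fiducial markers and one site. The response in each session is a paired dose comparison (Methods/Design), so these shared features enter every response from that patient. It is plausible that a patient in whom one correction improved the dose is more likely than another to benefit from the next correction.

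The chance of having an event may also differ between patients. Under Treatment delivery, either couch shift or MLC tracking may be used, and the treatment team may act at lower thresholds. Events may then cluster in some patients.

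The binomial calculation behind the stated figures counts 24 events as 24 independent pieces of information. If they carry less, the chance of declaring success at the futile rate of 1/3 is higher than stated, and the chance of detecting 2/3 is lower. The design has little slack: 0.0488 against 0.05.

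**Working it through.** **Inputs from the article.** Futile rate p0 = 1/3, target rate p1 = 2/3, 24 events in total, 10 events at the interim with futility at 4 or fewer, event rate 0.10, five sessions per patient, 48 patients.

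**Inputs assumed.** The ICC of response within patient (0.1 to 0.5) and the ICC of having an event (0 or 0.3). The article gives neither.

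**1. Reproducing the stated figures.** With X1 ~ Bin(10, p) and X2 ~ Bin(14, p) independent, the chance of rejecting is the sum over x = 5 to 10 of P(X1 = x) × P(X2 ≥ 12 − x).

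- At p = 0.333 the terms are 0.0203 + 0.0175 + 0.0085 + 0.0022 + 0.0003 + 0.0000 = 0.0488, as stated. Using exactly 1/3 gives 0.0492.
- At p = 2/3 the sum is 0.910, as stated.

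The figures therefore belong to a cut-off of 12 of 24 events. The printed cut-off of 16 does not give them. Read as 16 of 24 events, the type I error is 0.0008 and the power 0.60 at 0.67. Read as 16 of 48 in a single stage, the type I error is 0.55.

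**2. How many patients supply the events.** If events fall at random at 10%:

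- Patients with at least one event: 48 × (1 − 0.9^5) = 48 × 0.4095 = 19.7.
- Patients with two or more: 48 × (1 − 0.5905 − 0.3281) = 48 × 0.0815 = 3.9.
- Share of events from those patients: (0.5 − 0.3281)/0.5 = 34%.
- Event-weighted mean cluster size: 1 + 4 × 0.10 = 1.40.

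With an event ICC of 0.3 (beta-binomial), the weighted mean cluster size is 1 + 4 × (0.10 + 0.3 × 0.90) = 2.48, and about 13 patients supply the 24 events.

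**3. Design effect.** DE = 1 + (weighted mean cluster size − 1) × response ICC. For example, 1 + 0.40 × 0.5 = 1.20 and 1 + 1.48 × 0.5 = 1.74.

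**4. Operating characteristics of the 12/24 rule.** These come from beta-binomial simulation, accruing patients until 24 events are reached, with the futility stop treated as binding.

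| Events | Response ICC | DE | Type I error | Power at 2/3 |
|---|---|---|---|---|
| Independent (exact) | 0 | 1.00 | 0.049 | 0.91 |
| Spread at random, about 20 patients | 0.1 | 1.04 | 0.051 | 0.90 |
| | 0.3 | 1.12 | 0.057 | 0.89 |
| | 0.5 | 1.20 | 0.062 | 0.89 |
| Event ICC 0.3, about 13 patients | 0.1 | 1.15 | 0.057 | 0.89–0.90 |
| | 0.3 | 1.44 | 0.076 | 0.86 |
| | 0.5 | 1.74 | 0.092 | 0.83 |

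The type I errors use 100,000 runs each, so the simulation error near 0.05 is √(0.05 × 0.95/100,000) = 0.0007. The increase at ICC 0.1 with randomly spread events is real in direction but negligible in size.

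**The case against.** **The inflation is small at the planned event rate.** Only sessions with an intervention event enter the test, on average 24/48 = 0.5 per patient. If events are spread at random, most contributing patients supply a single event, and a type I error of 0.051 to 0.062 is tolerable in a phase II trial contrasting 1/3 with 2/3. This stands. The larger figures need two assumed correlations at once, and nothing in the article favours the high end.

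**The numbers concern an inferred rule.** They apply to 12 of 24, which the article does not print. Under 16 of 24, the type I error stayed at or below about 0.035 in every clustering scenario run. This also stands, and limits the point to the stated design figures. The optional wording of the futility stop is a further separate matter: if the stop is not binding, the 12/24 rule already has a type I error of 0.067 under independence.

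**The unseen analysis plan may handle clustering.** It may do so in the final model. It cannot change the operating characteristics printed here, which rest on an explicit independence assumption.

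**Stronger readings that the article does not support:**

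- A reader might infer that confidence intervals for the primary endpoint will be too narrow. The article plans no interval or standard error for that endpoint.
- A reader might take five sessions per patient as the working cluster size. If every session counted as an event, the type I error would be about 0.074 to 0.141 and power 0.86 to 0.75 for response ICC 0.1 to 0.5. MLC tracking adjusts the beam continually, but the article does not say that each tracked session is an intervention event, and it plans for 10%.
- A reader might infer that a few patients could decide the result. Even with event ICC 0.3, about 13 patients supply the events.

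**Conclusion.** The point holds for the stated design figures. They assume independence of sessions that are nested in patients, and any positive within-patient correlation of response makes 0.0488 too low and 0.91 too high. The direction is firm. The size depends on correlations that the article does not give: small if events are spread at random, and moderate if they also concentrate in some patients, where the type I error could approach twice its nominal value at the top of the assumed range. The sizes also assume the 12/24 rule with a binding futility stop. The mismatch between that rule and the printed cut-off of 16 is a separate and larger problem. It comes first, because the clustering figures have no meaning until the rule is settled.

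**What to change.** 1. Reconcile the printed cut-off with the stated error rates, and state whether the denominator is events or patients.
2. State the independence assumption as an assumption, and restate type I error and power for the reconciled rule over a declared range of response and event ICCs, such as the one tabulated above.
3. Report how many patients supply the events and how many events each supplies.
4. Accompany the binomial test with a patient-clustered analysis, for example a patient-level bootstrap or a beta-binomial model, and say in advance that the conclusion depends on it.

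**Cost.** Some added wording, one further analysis and slightly less favourable stated figures; no extra patients are needed for this. The limitation to acknowledge is that the ICC will be poorly estimated, because most clusters are expected to hold one event. The clustered result should therefore be read alongside the ICC range, not as a precise correction.

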### Analysis

An interim analysis will be performed after 20 patients have been accrued. This will correspond to an estimated 10 intervention events over 100 sessions. If four or fewer responses are observed in these 10 events, consideration will be given to the cause of the lack of response and the study may be stopped on the grounds of futility. At the same time, the IDSMC will review the trial for safety and determine whether or not it should continue. Otherwise, the study will continue with an additional 28 patients to be recruited. The main analysis will be performed after all 48 patients have completed treatment, with the final analysis being performed after the last patient has completed 2 years of follow up.

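### The rejection rule (16 responses in 48 patients) is not the rule behind the stated error rates, which belong to 12 or more of 24 intervention sessions

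*Protocol article*

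**What the plan says.** All the statements are in the protocol article.

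- **Unit and method (Sample size calculation):** "treating each treatment session as an independent event and then using Simon’s two-stage design".
- **Size (same section):** "a sample size of 24 sessions with intervention events will give us 90% power with 95% confidence".
- **Rates (same section):** the aim is to "rule in a success rate of 2/3 in favour of the futile rate of 1/3".
- **Conversion to patients (same section):** "we need 24/0.10 = 240 treatment sessions, which for the 5-session SBRT regime equals 48 patients".
- **First stage (Analysis):** the interim look follows the 20th patient. "This will correspond to an estimated 10 intervention events over 100 sessions". The futility condition begins "If four or fewer responses are observed in these 10 events", after which the study may be stopped.
- **Final rule (Sample size calculation):** "The null hypothesis will be rejected if 16 or more responses are observed in 48 patients".
- **Operating characteristics (same section, next sentence):** "This design yields a type I error rate of 0.0488 and power of 0.91 when the true response rate is 67" per cent.

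**The concern.** Every step of the design counts intervention sessions: 10 at the first stage and 24 in total. The 48 patients enter only as the number expected to supply those 24 sessions. The rejection sentence then changes the denominator to patients and gives a cut-off of 16. As a share of 48 that is the futile rate, and as a share of 24 it is the target rate. A cut-off placed at either rate would not be expected to give 5% type I error together with 91% power.

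This is the only decision rule given for the primary hypothesis. If the printed rule and the printed error rates belong to different designs, a result between the two cut-offs is positive under one sentence and negative under the next. The choice could then be made after the data are seen.

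**Working it through.** **Inputs**

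| Quantity | Value | Source |
|---|---|---|
| Null and target rates | p0 = 1/3, p1 = 2/3 | Sample size calculation |
| Total intervention sessions | n = 24 | Sample size calculation |
| First stage | n1 = 10 | Analysis |
| Futility boundary | r1 = 4 (stop at 4 or fewer) | Analysis |
| Final cut-off | r, the quantity under test | – |

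**Formula.** The probability of rejecting at true rate p is the sum, over first-stage counts x = 5 to 10, of P(Bin(10, p) = x) × P(Bin(14, p) ≥ r − x).

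**Reproducing the stated figures.** With p0 = 0.333, p1 = 0.667 and r = 12:

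- Type I error: 0.02027 + 0.01753 + 0.00846 + 0.00223 + 0.00030 + 0.00002 = 0.0488.
- Power: 0.12842 + 0.22344 + 0.25921 + 0.19535 + 0.08700 + 0.01743 = 0.911.

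Both match the protocol. Exact thirds give 0.0492 and 0.910, so the fourth decimal suggests that the rates were entered as 0.333 and 0.667.

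**Other cut-offs, same first stage (0.333 and 0.667)**

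| Reject at | Type I error | Power |
|---|---|---|
| 11 or more of 24 | 0.087 | 0.920 |
| **12 or more of 24** | **0.0488** | **0.911** |
| 13 or more of 24 | 0.023 | 0.885 |
| 16 or more of 24 | 0.0008 | 0.589 |

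The neighbouring cut-offs do not fit. A search of two-stage designs with 15 to 30 events found one other design with type I error 0.0488 and power within two points of 0.91. It stops at 7 or fewer of 16, then rejects at 11 or more of 21, with power 0.927. It matches neither the stated total of 24 nor the stated first stage of 10.

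**Can 16 of 24 be rescued by another first stage?** A futility stop can only lower power, so the single-stage value is the ceiling: P(Bin(24, 2/3) ≥ 16) = 0.594. Taking the target as 0.67 raises it to 0.608.

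**Literal reading, 16 of 48.** 16/48 = 1/3. With 48 independent units, P(Bin(48, 1/3) ≥ 16) = 0.554, or 0.531 with a stop at 4 or fewer of the first 20. Power is close to 1.

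**Results that change sides.** At a true rate of 0.667, the probability of passing the first stage and finishing with 12 to 15 responses is 0.911 − 0.589 = 0.32.

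**The case against.** The strongest reply is that the number of patients in the rejection sentence names the enrolled cohort, not a binomial denominator. Responses can arise only in sessions with an intervention event, and 48 patients are expected to supply about 24. On that reading the rule is 16 of about 24. It is conservative, and the 0.55 false-positive figure never arises. This is fair: 0.55 belongs to the literal reading only, and the more likely harm is lost power. The mismatch remains, because 16 of 24 gives 0.0008 and 0.59.

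A second reply is that 12 appears nowhere in the article, while 16 is exactly 2/3 of 24 and may have been chosen on purpose. That cannot be excluded. In that case the error rates are the wrong part, and one of the two sentences still has to change.

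Third, 0.0488 depends on enforcing the 4-of-10 stop, whereas the Analysis section only says that the study may stop. If the stop is ignored, 12 of 24 gives a type I error of about 0.068 (0.0677 with exact thirds) and power 0.97. This stands as a condition on the fix and does nothing for a cut-off of 16.

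Fourth, 10 and 24 are expected counts. With the cut-off kept at 12 and the same first stage, 20 realised events would give type I error 0.012 and power 0.79, and 28 would give type I error 0.102. This is a real but separate matter, which the corrected wording could also cover.

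An unseen analysis plan is no answer, because the article itself prints the rule and its error rates side by side.

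**Conclusion.** The concern holds. The stated type I error and power are those of rejection at 12 or more of 24 intervention sessions with a 4-of-10 futility stop. They are not those of the printed rule on either denominator. Read as 16 of 24, the rule has 59% power at the target rate, a false-negative risk of 41% against the stated 9%. Read as 16 of 48, it has a type I error of 0.55.

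The figures assume independent sessions, as the protocol does, exactly 10 and 24 realised events, and an enforced first-stage stop. Moving the target from 2/3 to 0.67 changes the power of the 16-of-24 rule only from 0.588 to 0.602. Because this is the decision threshold of the primary test, it must be corrected before the analysis.

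**What to change.** Replace the rejection sentence with: *The null hypothesis will be rejected if 12 or more responses are observed in 24 intervention sessions (10 at stage 1, stopping at 4 or fewer).* Keep 0.0488 and 0.91.

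The sponsor should confirm that this is the intended design. If 16 of 24 was meant, keep that cut-off, name intervention sessions as the denominator, and restate the type I error as 0.0008 and the power as 0.59.

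Two points should be settled with the new wording:

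- 0.0488 requires the first-stage stop to be binding. Either the Analysis section says so, or the type I error without the stop (about 0.068) is reported beside it.
- The plan should say how the cut-off is set if 48 patients yield a number of intervention sessions other than 24.

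The core correction is one sentence, repeated in the full protocol and SAP if they carry the same rule. The two further points need a few more lines. Patient numbers, visits and procedures do not change.
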